### Interim analyses {21b}

No interim analyses are planned.

### Methods for additional analyses (e.g. subgroup analyses) {20b}

Full plans for subgroup analyses will be codified in the statistical analysis plan prior to database lock.

### Methods in analysis to handle protocol non-adherence and any statistical methods to handle missing data {20c}

Many participants will not complete all 4 surveys; however, the longitudinal models planned for the primary analyses above should account for this. When appropriate, multiple imputation will be used. Exploratory analyses may focus on how many physicians at a site used the CME intervention and if possible, we will conduct analyses evaluating the primary outcome within the subset of physicians who viewed the CME.

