##### Sample size revised

After initiating a process change allowing patients to self-enroll into the study, recruitment in the patient level intervention accelerated. The trial leadership, in consultation with the independent medical monitor and a representative from the sponsoring institute, elected to increase the maximum sample size for this group, to ensure adequate sampling before and after the provider level intervention in each site. The increased size also allows for increased power in important subgroups (fully specified in the statistical analysis plan). Patients with either BPPV or vestibular neuritis may represent as little as 20% of the overall cohort and we anticipate most of the benefit of the patient level intervention will be in these groups. Finally, we felt that there was a low risk of having excess power. The risk of demonstrating a numeric difference in the DHI that is not clinically relevant was considered low. In addition, the non-response patterns of participants across the 4 weeks of follow up surveys for the DHI introduce another issue that could reduce the effective power of the trial. This operational decision to increase sample size was made by the trial leadership, who did not have access to the outcome data by treatment assignment at the time of the decision. Based on enrollment projections, the maximum allowed sample size was set at 2000 (based on the plan for 6 months of recruitment following the last site level intervention), although the most likely final sample size is around 1500. In addition, the standard deviation of the DHI was higher than expected—therefore power was likely lower than our pre-trial assumptions.

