## Statistical methods

### Statistical methods for primary and secondary outcomes {20a}

The primary outcome is the dizziness handicap inventory (DHI) which is a continuous (0–100) measure of dizziness disability based on a patient’s responses to 25 survey questions. Higher scores indicate more disability. We will use the Ceballo validated Spanish translation for the Spanish speaking individuals. As a sensitivity analysis, we will substitute 2 Lopez questions because we did not think the Ceballo translation was optimal for the following questions: Does bending over increase your problem? (Ceballo: When you get up, does your problem increase?]-Does turning over in bed increase your problem? (When you get out of bed, does your problem increase?] The DHI outcome will be obtained at 1-week intervals after the ED visit for 4 consecutive weeks—corresponding to 4 assessments. We will obtain 4 weekly assessments as we expect that time to recovery will vary given our heterogenous dizziness population. The primary analysis will be a multi-level model as follows: dependent variable (outcome) is the DHI (continuous); fixed independent variables are ED-level intervention group (0/1), patient intervention group (0/1), an interaction term of ED-level intervention with patient intervention group, patient severity at the time of ED visit (continuous), and assessment number (categorical, 1–4); and including a random ED-level intercept. This method allows us to capture variability in recovery over time while maintaining all of the variation in our continuous outcome. We include the severity at the time of the ED visit measure in the model to adjust for baseline disability, protecting against any random imbalances. Because of the two concurrent interventions (ED-level [0/1], patient-level [0/1]), patients will be in either a no intervention group, an ED-level intervention group only, a patient-level intervention group only, or both an ED- and patient-level intervention group. For a secondary analysis, we will add an interaction term of assessment number and intervention group (i.e., a 3-way interaction term of ED-level intervention, patient-level intervention, and assessment number) to further evaluate if any association of intervention group with the DHI outcome is modified by time to assessment. We will make comparisons of the effectiveness of the intervention at each time interval by estimating average marginal effects from our secondary model and comparing marginal effects using Wald Tests. We do not anticipate that our interventions will have differential effects by sex, either at the patient or provider level. Dizziness presentations in the emergency department are more common in females, although at this point there is little biological understanding of the reason for this. For the patient level analyses, we will disaggregate the data and perform analyses separate for male and female patients to assess for heterogeneity. In secondary analyses, we will explore if patient factors (age, sex, Charlson co-morbidities, health literacy) modify the effect of interventions with the outcome. Health literacy will be measured at the first outcome assessment using the BRIEF health literacy tool, 80 which was selected using the Boston University Health Literacy Tool Shed.

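### The primary DHI model has no week-specific treatment effects and no patient-level term, so the statement that it should account for missed weekly surveys is not assured

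*Protocol article*

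**What the plan says.** Item 20a of the protocol article sets the schedule: "The DHI outcome will be obtained at 1-week intervals after the ED visit for 4 consecutive weeks". It then writes out the primary model. Besides the two group indicators, the fixed effects are "an interaction term of ED-level intervention with patient intervention group, patient severity at the time of ED visit (continuous), and assessment number", followed by "and including a random ED-level intercept". There is no group-by-assessment term, and no patient-level random effect or within-patient covariance is listed.

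Effects that differ by week appear only afterwards: "For a secondary analysis, we will add an interaction term of assessment number and intervention group". Week-by-week marginal effects are to be taken from that secondary model.

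On missing surveys, item 20c says: "Many participants will not complete all 4 surveys; however, the longitudinal models planned for the primary analyses above should account for this". It adds that multiple imputation will be used where appropriate, without saying when. The section on the revised sample size mentions non-response as a threat to power: "the non-response patterns of participants across the 4 weeks of follow up surveys for the DHI introduce another issue". No response rate by week is given anywhere.

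**The concern.** A likelihood-based longitudinal model handles missing surveys under missing-at-random if its mean and its within-patient covariance are adequately specified. The printed model leaves a gap in each.

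- **Mean.** One materials effect per ED period is imposed on all four weeks. If the true effect changes over the weeks and response differs by week, the estimate depends on how many people answered each survey, even when surveys are missing completely at random.
- **Covariance.** With only an ED intercept, the four surveys of one patient are treated as independent given ED and covariates. The model then cannot use a patient's earlier scores to allow for who drops out.

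The abstract describes the patient-level primary outcome as the DHI across the four weeks. The reported number could be smaller or larger than that effect, depending on the response pattern, while readers are told that missed surveys are dealt with.

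**Working it through.** **The plan's own figure.** The only related figure is the power of 0.97 for 42 vs 35.7, SD 16, 200 per group. SE = 16 × √(2/200) = 1.6; 6.3/1.6 = 3.94; power = Φ(3.94 − 1.96) = 0.976. This ignores the stated ICC, which is a separate matter. The calculation treats the DHI as a single outcome without weeks or missing surveys, so it does not bear on this point.

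**Assumptions (not in the documents).** Response at weeks 1–4 of 85/70/60/50%, the same in both arms. Effect profiles with a four-week mean of 3.15 points, half the 6.3-point design difference. Within-patient correlation ρ = 0.5 where a patient term is used. ED variation is left out of the weights.

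**Weights, model as printed.** With week as a category and surveys treated as independent, week t has weight r_t / Σr, where r_t is its response rate. Σr = 0.85 + 0.70 + 0.60 + 0.50 = 2.65.

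**Weights with a patient random intercept, monotone drop-out.** A patient with k surveys gives each one weight 1/(1 + (k − 1)ρ), which is 1, 0.667, 0.5 and 0.4 for k = 1 to 4. The shares with k = 1 to 4 are 0.15, 0.10, 0.10 and 0.50. The unscaled weights are:

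- week 4: 0.50 × 0.4 = 0.200
- week 3: 0.200 + 0.10 × 0.5 = 0.250
- week 2: 0.250 + 0.10 × 0.667 = 0.317
- week 1: 0.317 + 0.15 × 1 = 0.467

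Divided by their sum, 1.233, they are 0.378, 0.257, 0.203 and 0.162 for weeks 1 to 4. The tilt is stronger than for the printed model because an early drop-out's only survey keeps full weight.

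| Effect, weeks 1–4 | As printed | With patient intercept |
|---|---|---|
| 0 / 2.1 / 4.2 / 6.3 | (1.47 + 2.52 + 3.15)/2.65 = 2.69 (86%) | 2.41 (77%) |
| 6.3 / 4.2 / 2.1 / 0 | (5.355 + 2.94 + 1.26)/2.65 = 3.61 (114%) | 3.89 (123%) |
| 2.1 / 2.8 / 3.5 / 4.2 | (1.785 + 1.96 + 2.1 + 2.1)/2.65 = 3.00 (95%) | 2.90 (92%) |
| 3.15 each week | 3.15 (100%) | 3.15 (100%) |

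**Range over response patterns, steep rise.**

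- 85/75/65/60%: as printed 8.085/2.85 = 2.84 (90%); with a patient intercept 83%.
- 80/60/50/40%: as printed 5.88/2.30 = 2.56 (81%); with a patient intercept 70%.
- Rising response, 60/70/80/90%: as printed (1.47 + 3.36 + 5.67)/3.00 = 3.50 (111%), so the tilt reverses.
- Full response: weight 0.25 each week, so no tilt.

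**Missing-at-random drop-out with a constant effect.** Simulation of 600,000 patients per scenario: true effect 6.3, SD 20, correlation 0.6, drop-out depending on the previous observed DHI.

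| Model | Same mechanism in both arms | Opposite direction by arm |
|---|---|---|
| As printed (no patient term) | 5.9 | 2.4 |
| Group-by-week terms only | 5.8 | 1.4 |
| Patient intercept only | 6.4 | 6.3 |
| Both | 6.4 | 6.3 |

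The second column is an extreme mechanism. With both additions, the equally weighted mean was 6.2–6.4 against 6.3 in every scenario: constant, growing or fading effect, with complete data, data missing completely at random, or drop-out at random given the last DHI.

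**Cost in precision.** As printed, the variance of the equally weighted mean relative to the single coefficient is (1/16)(1/0.85 + 1/0.70 + 1/0.60 + 1/0.50) ÷ (1/2.65) = 0.392/0.377 = 1.039, so the standard error rises about 2%. With a patient term, 1,500 patients, SD 20 and ρ = 0.5, it goes from 0.93 to 0.94, about 1%.

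**The case against.** Several stronger readings are tempting, and the documents do not support them.

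- **That the plan expects the effect to differ by week.** Its reason for weekly surveys is that "we expect that time to recovery will vary given our heterogenous dizziness population". That concerns how fast patients recover. Whether the effect changes with time is left as an open question for the secondary model.
- **That the estimate will lean to the early weeks.** No response rates are given, and nothing says that response falls. Falling response is plausible but assumed.
- **That the missing-data statement is untrue.** The article says only that the models should account for missed surveys. With a constant effect and surveys missing completely at random, they do. Re-weighting the weeks changes which average is estimated, and no passage defines that average as equally weighted.
- **That power drops materially.** For the steep rise, 2.41/0.93 gives power 0.74, against 0.92 for the equally weighted mean. That takes the steepest profile, half the design difference, a patient term the printed model lacks, and all 1,500 patients without the ED-by-patient interaction. The milder rise gives 0.88 against 0.92. The steep shape with a mean of 6.3 gives 0.999 against 1.000.

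It is also fair that weekly effects are already planned as a secondary analysis, and that the SAP, which is not shown, may add a within-patient covariance. Multiple imputation that carried earlier scores and week-specific group effects could close both gaps.

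What stands: item 20a writes the primary model out in full without either element, item 20c rests on that model, and imputation has no trigger. A secondary analysis does not change what the primary coefficient estimates.

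**Conclusion.** The concern holds as a matter of assurance: the printed primary model does not secure what item 20c says of it. Two conditions, both assumed here, are needed for the weighting problem: an effect that varies by week and response that varies by week. In the 85/70/60/50% examples the printed model's coefficient is then 86% to 114% of the four-week mean, or 77% to 123% with a patient random intercept, and only 95% and 92% for the milder rise. Because the ED-by-patient interaction is in the model, the same weighting applies separately within each ED period.

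The missing patient-level term is a second gap that needs neither condition. Drop-out that depends on earlier observed DHI biases the printed model even with a constant effect: slightly in the plain case (5.9 against 6.3) and severely if the mechanism runs in opposite directions by arm (2.4).

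**What to change.** 1. Include in the primary model the group-by-assessment terms: patient materials × week, ED-level × week and their three-way term, as the secondary model already intends.
2. Add a patient-level random effect or a within-patient covariance. The week terms alone are not enough: without it they gave 2.82 against a constant 3.15 in a further simulation of missing-at-random drop-out.
3. Define the primary effect as the equally weighted mean of the four weekly contrasts, and name the ED period it refers to.
4. Keep the constant-effect model as a sensitivity analysis.
5. Reword item 20c to say that missed surveys are handled under missing-at-random for that model.

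No new data are needed, and the standard error rises by about 1–3%. The change does redefine the primary effect. Enrolment ended in March 2025 and the analysts are not blinded, so it has to be documented before results by treatment group are examined.

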### Plans to give access to the full protocol, participant level-data and statistical code {31c}

The protocol and statistical code will be available online after publication of the main manuscript. Participant level data (with identifiers removed) may be available, under the conditions of sufficient funding by a qualified requester trained in human subject confidentiality protocols and with proper data use agreements between all institutions that govern data access, story and short- and long-term use.

## Oversight and monitoring

### Composition of the coordinating centre and trial steering committee {5d}

The coordinating center will be comprised of the multiple PIs and key co-investigators from neurology, stroke, physical therapy, health intervention design, and biostatistics. The multiple PIs in conjunction with the project manager will meet weekly with the enrolling and follow-up staff to coordinate the day-to-day operation of the trial.

### Composition of the data monitoring committee, its role and reporting structure {21a}

In accordance with sponsor guidelines and low risk level of study, a single independent medical monitor (IMM) with expertise in neuro-otology oversees the safety of the trial. The IMM regularly reviews the protocol, accrual information, outcomes and adverse events by treatment group and provides advice to the investigators and the sponsoring institute regarding trial continuation.

### Adverse event reporting and harms {22}

An adverse event (AE) is any unfavorable and unintended sign (including a clinically significant abnormal laboratory finding), symptom, or disease temporally associated with the use of a medical treatment or procedure regardless of whether it is considered related to the medical treatment or procedure (attribution of unrelated, unlikely, possible, probable, or definite). Each AE is a unique representation of a specific event used for medical documentation and scientific analysis.

A serious adverse event (SAE) is an AE that is fatal or life threatening, is permanently or substantially disabling, requires or prolongs hospitalization, results in a congenital anomaly, requires intervention to prevent permanent impairment or damage, or any event that the treating clinician or internal medical monitor judges to be a significant hazard, contraindication, side effect, or precaution. Reporting serious adverse events (SAEs) are based on the guidelines of the International Conference on Harmonization (ICH).

For the purposes of the trial, we will only capture patient level AEs and SAEs that are possibly, probably or definitely related to the performance of BPPV care processes (Dix-Hallpike test or Canalith Repositioning Maneuver).

Events will be captured for the ED focused intervention by screening the medical records using natural language processing complemented by manual review of visits with DHT/CRM documentation, and subsequent medical visits with the primary diagnosis of the adverse events. For the patient facing intervention, adverse events will be captured using the same mechanisms as above, plus additional capture from patient surveys at the outcome assessment. The principal investigators are responsible for designating, at the time an AE is reported, how likely it is that the AE was caused by the study intervention. These decisions (classification of relatedness) will be reviewed by the IMM. This determination requires clinical judgment, but for purposes of this study an algorithm is used to help the investigators provide reporting that is as objective as possible and consistent with reporting across the trial.

### Frequency and plans for auditing trial conduct {23}

The statistical team frequently reviews data from the trial and performs validity and outlier checks.

### Plans for communicating important protocol amendments to relevant parties (e.g. trial participants, ethical committees) {25}

The clinical coordinating center will propose any protocol amendments first to the institute and the IMM. After feedback and approval from these bodies, the IRB of record will receive a protocol amendment via their submission system.

### Dissemination plans {31a}

The primary dissemination plan is via publication of the main manuscript. Should the intervention be effective, KPSC plans to consider making elements of the physician and patient facing resources persistent and available to their members. The results will be posted to clinicaltrials.gov in accordance with the requirements of the National Institutes of Health.

## Discussion

The DIZZTINCT-2 trial addresses key areas of uncertainty in how to improve the care of emergency department patients with acute vertigo. The design incorporates a large, pragmatic, health system focused intervention along with a smaller, patient focused self-care intervention in a stepped-wedge design with an embedded individually patient randomized clinical trial. The first DIZZTINCT trial demonstrated that ED physicians could be intervened upon to do more physical examination (DHT and CRM) and less low value imaging. Major areas where more data was needed following the first DIZZTINCT trial included patient-oriented outcomes, along with tools to address diagnoses other than benign positional vertigo such as vestibular neuritis and migraine. In addition, follow up data on how much and how fast patients improved was needed. DIZZTINCT-2 will address these key knowledge gaps efficiently.

## Trial status

The trial is operating under Protocol Version 3. Patient enrollment started in November 2022—and the last participant included was enrolled in March 2025. The last follow up of secondary outcomes was anticipated in June 2025 (because not all stroke cases would be immediately coded—the full data for this secondary outcome measure was not available until later in summer 2025). The health system focused aim included patients before and after the individually randomized patient focused aim. This manuscript was delayed in submission due to attempts to train generative artificial intelligence (AI) large language models to reformat the scientific protocol document, based on prior Trials publications where there were also publicly available scientific protocols. The AI model made promises, and at times would work for several weeks noting it was close to producing an algorithm that could accomplish this. It turns out it was incorrect. The first author would recommend against using AI models to reformat scientific protocols into the Trials SPIRIT template.

## Data Availability

The multiple principal investigators will have access to the final trial dataset. Access of this dataset to others will be governed by the sponsoring health system.

## Abbreviations

AE: Adverse event
BPPV: Benign paroxysmal positional vertigo
CI: Confidence interval
CME: Continuing medical education
CRM: Canalith repositioning maneuver
CT: Computed tomography
DHI: Dizziness handicap inventory
DHT: Dix-Hallpike test
ED: Emergency department
EMR: Electronic medical record
GLM: Generalized linear model
ICC: Intraclass correlation coefficient
ICH: International conference on harmonization
IMM: Independent medical monitor
IRB: Institutional review board
KPSC: Kaiser Permanente Southern California
MIC: Minimal clinically important change
NIH: National Institutes of Health
PHQ: Patient Health Questionnaire
PRO: Patient reported outcome
RCT: Randomized controlled trial
SAE: Serious adverse event
SD: Standard deviation
SPIRIT: Standard Protocol Items: Recommendations for Interventional Trials
